**Methods:**

Guided by the Health Disparities Research Framework and the Practical, Robust Implementation and Sustainability Model, we will conduct a quasi-experimental study with four primary care clinics within a large health system (MedStar Health). Individuals eligible for lung cancer screening, defined as 50–80 years old, ≥ 20 pack-years, currently smoking, or quit < 15 years, no history of lung cancer, who have an appointment scheduled with their provider, and who are non-adherent to screening will be identified via the EHR, contacted, and enrolled (*N* = 184 for implementation clinics, *N* = 184 for comparison clinics; total *N* = 368). Provider participants will include those practicing at the partner clinics (*N* = 26). To increase provider-prompted discussions about lung screening, an electronic health record (EHR) clinician reminder will be sent to providers prior to scheduled visits with the screening-eligible participants. To increase patient-level knowledge and patient activation about screening, an inreach specialist will conduct a pre-visit phone-based educational session with participants. Patient participants will be assessed at baseline and 1-week post-visit to measure provider-patient discussion, screening intentions, and knowledge. Screening referrals and screening completion rates will be assessed via the EHR at 6 months. We will use mixed methods and multilevel assessments of patients and providers to evaluate the implementation outcomes (adoption, feasibility, acceptability, and fidelity).

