## Methods/design

### Study aims

This study will target provider- and patient-level barriers in order to improve utilization of lung screening and to achieve equity in screening rates by conducting a quasi-experimental study comparing a Multilevel Intervention to Usual Care. The Multilevel Intervention will perform inreach to educate patients about screening prior to their visit. At the same time, an EHR communication tool, similar to email, will send a reminder to primary care providers prior to scheduled visits with screening-eligible patients.

The *specific aims* of the trial are to (1) test the impact of the multilevel strategies on primary outcomes (provider-patient discussion, screening intentions, and knowledge) and secondary outcomes (screening referrals and screening completion rates) and (2) evaluate the implementation outcomes (adoption, feasibility, acceptability, fidelity).

The *hypotheses* are (1) participants in the Multilevel Clinics who receive the provider- and patient-level strategies will be significantly more likely to report having a screening discussion, intending to be screened, and having greater knowledge compared to the Comparison Clinic participants; (2) the multilevel, bundled strategies will increase screening referrals made by providers in the Multilevel Clinics; and (3) completion rates among the participants will be higher among the Multilevel Clinic participants compared to the Comparison Clinic participants. Finally, we will explore whether Health Disparities Framework factors (e.g., race, education, health literacy) moderate the outcomes (e.g., we expect that African Americans will have significantly greater knowledge in the Multilevel Clinics vs. the Comparison Clinics, whereas the strategies will have less of an impact among Whites).

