### Clinical setting and healthcare provider participants

MedStar Health, the largest not-for-profit health system in the Mid-Atlantic, includes more than 300 care locations including more than 60 ambulatory care centers, and primary and specialty care in academic medical centers and community-based clinics, 10 hospitals, and 33 urgent care clinics located in Baltimore, MD, Washington, DC, and Northern VA. This health system provides care to a diverse community which includes a large Black or African American population (44–73% in the participating clinics), and uninsured or underinsured individuals.

We will conduct the quasi-experimental study in partnership with four primary care, community-based ambulatory clinics within the MedStar Health system, matched on CT scanner on site (yes/no) and minority representation (> 40% Black or African American; Fig. 2). Clinic eligibility criteria include (1) clinic providers use the Message Center within MedConnect (Oracle Cerner); (2) > 400 patients who are 50–80 years old with a documented smoking history in the last 12 months; (3) > 40% African American patient population; and (4) a site champion who will serve as the primary point of contact for this study. The provider sample includes full- and part-time primary care providers at the participating clinics.

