### Patient recruitment and procedures

During the recruitment period, the research assistants will access the list of potentially eligible individuals from an EHR report that our team developed to identify patients with an upcoming visit who are 50–80 years old with an ever-smoking history. Due to the limitations of the EHR smoking history data, including a large number of missing data for the pack-years field (90% on average are missing pack-years), we are conservatively estimating 25% of those reached will be eligible for the study (Fig. 2). The report utilizes EHR appointment and clinical data and will be imported into the study’s REDCap database weekly by the study team. Our team will invite patients to participate in the study through a mailed invitation letter, email, and the myMedStar patient portal, followed by phone calls (up to 3 attempts). During this call, the research staff member will describe the study, determine eligibility, obtain verbal consent, and complete the baseline assessment. We expect to enroll *n* = 184 in the Multilevel Clinics and *n* = 184 in the Comparison Clinics (total *N* = 368).

Following baseline (T0), Multilevel Clinic participants will receive the phone-based inreach and education within 1 week to 3 days prior to the visit. The comparison clinics will not receive the bundled strategies, but eligible participants will be enrolled and followed to measure the outcomes. All patient participants will receive up to $50 in total for their participation.

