### Statistical analysis plan

We will examine the distributions of all variables to describe the characteristics of the study population. We will conduct analyses using *t*-tests, *χ*^2^ tests, and Pearson or Spearman correlation coefficients to assess the bivariate associations between the baseline characteristics and the outcome variables. Bivariate analyses will also be conducted to assess the associations between the study arm and baseline characteristics. Owing to any significant differences detected at the 0.05 level, the variables associated with both the study arm and the outcome of interest will be entered as covariates in subsequent analyses. To test the overall difference between the study arms on the primary outcomes, we will conduct logistic regression models (for provider-patient discussion — yes/no, screening intentions — likely/unlikely) and a linear regression model (for the screening knowledge score). Logistic regression analyses will also be conducted on the secondary screening outcomes (lung screening referral — yes/no, lung screening completion — yes/no). This study will explore potential moderators (e.g., race, health literacy, smoking status). That will be done by evaluating the presence of interactions between the moderators and study arm, one at a time, after adding them to the regression models described above. In sensitivity analyses, we will evaluate the robustness of our findings by using versions of the above models with generalized estimating equations (GEE). These models will use the sites as clusters, and assume an exchangeable working correlation structure.

For the qualitative analysis, we will use a deductive thematic analysis based on a priori PRISM constructs, with additional codes added as needed. Initial codes will be generated by two coders and each of the coders will review two transcripts for each sub-population (i.e., patient and provider) to reach a consensus on the coding framework and application of codes prior to splitting up the remaining transcripts.

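### The exploratory race-by-arm models have no clinic term, so clinic differences can pass for racial moderation if clinics within an arm differ in both racial mix and outcome

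*Protocol article*

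**What the plan says.** Under Statistical analysis plan, the article states the main models: "we will conduct logistic regression models (for provider-patient discussion — yes/no, screening intentions — likely/unlikely) and a linear regression model" for the knowledge score. Covariates are chosen by a screening rule: "the variables associated with both the study arm and the outcome of interest will be entered as covariates in subsequent analyses". Moderation is then tested by "evaluating the presence of interactions between the moderators and study arm, one at a time, after adding them to the regression models described above". No clinic term is named in any of these models. The same section describes the moderation work as exploratory. It adds a sensitivity analysis that refits the models by GEE, with sites as clusters and an exchangeable working correlation.

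Study aims gives the purpose: "we will explore whether Health Disparities Framework factors (e.g., race, education, health literacy) moderate the outcomes". The example there expects a gain in knowledge among African American participants and a smaller effect among White participants.

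Clinical setting and healthcare provider participants reports a "large Black or African American population (44–73% in the participating clinics"). The clinics are "matched on CT scanner on site (yes/no) and minority representation (> 40% Black or African American; Fig. 2"). The same threshold is also a clinic eligibility criterion. Recruitment is to reach "184 in the Multilevel Clinics and *n* = 184 in the Comparison Clinics (total *N* = 368"). The text does not say which clinics are in which arm; the study-flow figure is not available here.

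**The concern.** Matching on a threshold that every eligible clinic must already pass leaves the racial mix free to vary between clinics. Where two clinics in one arm differ in mix, that arm's African American and White patients come from the two clinics in different proportions. A model with arm, race and arm-by-race but no clinic then attributes part of any outcome difference between those clinics to race within that arm. Unless the other arm has a matching distortion, the remainder appears as arm-by-race interaction.

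The general limit of a four-clinic quasi-experiment does not cover this. The arm effect cannot be separated from clinic. The arm-by-race effect can be estimated inside clinics, because each clinic serves both groups, and the stated model does not use that. At stake is whether a report that the strategies narrow or widen a racial gap reflects race or only where patients receive care. The distortion can also hide a real difference.

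**Working it through.** **Inputs from the article.** Four clinics; African American share 44–73%; 184 patients per arm; significance level 0.05 (taken as two-sided).

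**Assumptions.** Two clinics per arm with 184 / 2 = 92 patients each; two race groups; enrolled mix equal to the clinic mix; no racial difference within any clinic; no strategy effect.

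**The plan's own moderation figure.** Sample size and power claims more than 80% power for an effect size of 0.50 in equal subgroups. For an arm effect inside one subgroup of 92 per arm, power is Φ(0.50/√(2/92) − 1.96) = 92%, so the claim reproduces on that reading. Read as an interaction of 0.50, it is Φ(0.50/√(4/92) − 1.96) = 67%. Neither figure depends on the clinic term.

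**Step 1: how much of a clinic gap leaks.** Put clinics at 44% and 73% in one arm with equal enrolment. The share of patients from the 73% clinic is:
- African American: 0.73 / (0.44 + 0.73) = 0.624
- White: 0.27 / (0.56 + 0.27) = 0.325

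The difference, 0.30, is the fraction of the outcome gap between the two clinics that enters that arm's race contrast. With a 30:70 enrolment split, in either direction, it is 0.24–0.27.

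**Step 2: spurious difference and false rejection.** Let completion be 10% in the first-listed clinic of each arm and 30% in the second. In the 44/73 arm, African American completion is 0.624 × 30% + 0.376 × 10% = 22.5% and White completion is 0.325 × 30% + 0.675 × 10% = 16.5%, a gap of 6.0 points. The gap in the other arm follows in the same way. For 62/55, the second-clinic shares are 0.55/1.17 = 0.470 and 0.45/0.83 = 0.542, a gap of −1.4 points. Rejection rates are from simulated null trials of 4 × 92 patients analysed by logistic regression.

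| Multilevel clinics (% African American) | Comparison clinics | Spurious race-by-arm difference (points) | Rejection, no clinic term | Rejection, clinic indicators |
|---|---|---|---|---|
| 44/73 | 73/44 | 6.0 + 6.0 = 12 | about 28% | about 5% |
| 44/73 | 62/55 | 6.0 + 1.4 = 7.4 | about 14% | about 5% |
| 44/73 | 55/62 | 6.0 − 1.4 = 4.6 | about 8% | about 5% |
| 44/73 | 44/73 | 6.0 − 6.0 = 0 | about 5% | about 5% |
| 44/55 | 62/73 | 2.2 − 2.5 = −0.3 | about 5% | about 5% |

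**Step 3: smaller clinic gaps.** In the reversed layout (first row), rejection without a clinic term is 12–13% for completion of 10% and 20%, and 6.7% for 10% and 15%. In the second-row layout it is 7.8% and 5.5%.

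**Step 4: continuous outcome, such as knowledge.** Without a clinic term:
- One arm mixed (44/73), clinic gap 0.3 SD: bias 0.09 SD, rejection 7%. Gap 0.5 SD: 0.14 SD and 9.5%.
- Both arms mixed with opposite gaps of 0.3 SD: 0.19 SD and 15%. Gaps of 0.5 SD: 0.29 SD and 26%.
- Gaps in the same direction, or equal mix within each arm: no bias, 5%.

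With clinic indicators the bias stays within 0.01 SD and rejection is 4–6% in every scenario.

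**Step 5: the GEE sensitivity analysis.** In a small simulation (200 replicates, some non-convergence), exchangeable GEE cut the bias from 0.29 to about 0.03 SD, from 0.19 to 0.08 and from 0.14 to 0.05. In the weakest scenario it left 0.09 unchanged. In a separate run of 300 fits per scenario with default robust standard errors, its interaction test rejected a true null 29–38% of the time when clinics differed and 44% when they did not.

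**The case against.** The strongest reply is that the plan does bring clinic in. The GEE versions follow directly after the moderation sentence and can naturally be read as covering the interaction models. That stands as a correction to any suggestion that clinic is ignored throughout, and GEE did reduce the bias in most scenarios. It does not settle the matter. The text does not name the interaction models, and both the exchangeable correlation and the robust standard errors would rest on four sites.

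A reader might infer that clinic differences will be reported as racial moderation, or that the equity result is invalid as planned. The article does not support that. Leakage needs clinics within an arm to differ in both mix and outcome, without cancelling. The clinic-to-arm layout is not in the text, and no clinic-level outcome rates are given. The 44–73% range describes clinic populations, not enrolled patients, and Measures defines three race categories rather than two. The 28% is close to a worst case: both extremes in each arm, reversed pairing, and a 20-point completion gap.

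It is also fair that moderation is exploratory and in neither specific aim, and that the Discussion calls the results preliminary and concedes limited causal inference. This lowers the weight of the point. It does not make the model without a clinic term the better choice.

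**Conclusion.** The point holds as a conditional risk with a cheap remedy. The stated race-by-arm model can take clinic differences for racial moderation. Under the assumptions above, false rejection at a nominal 5% runs from about 5%, through 7–14% for moderate layouts or a 10%/20% clinic gap, to about 28% at the extreme. Where the trial falls in that range depends on the clinic layout and clinic outcome rates, which the sponsor knows or will observe and the text does not give. Clinic indicators hold the rate at about 5% in every layout examined, so the change is worthwhile whichever layout applies. This is a cheap improvement to an exploratory analysis. It is not a flaw in the primary comparison.

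**What to change.** State that in the race moderation models the arm main effect is replaced by indicators for the four clinics, which absorb arm, while the race and arm-by-race terms are kept. The same form may be used for smoking status, health literacy or another moderator if its distribution differs by clinic; the article gives no evidence that it does. Present the GEE fit as secondary to this model for the interaction.

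The cost is one sentence of analysis text, an interaction standard error about 1–8% larger, and no arm main effect in that model, which the primary model still supplies. The change does not remove everything. Variation between clinics in how the strategies work is only partly dealt with: the part shared by both race groups goes into the indicators, but a racial gap that itself varies from clinic to clinic stays in the arm-by-race estimate. The report should say so.

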## Discussion

Guided by the Health Disparities Research and PRISM frameworks that take into account the multilevel determinants of cancer screening disparities and the multilevel interactions needed to understand and address these disparities, this quasi-experimental study will test the effect of provider- and patient-level implementation strategies to improve patient-provider discussion about lung screening and increase equity in lung screening rates between African American and White primary care patients. Through mixed-methods and multilevel assessments, this study is well-positioned to evaluate the impact of a provider prompt as well as a patient inreach and education component on the adoption of lung screening as an evidence-based intervention.

The planned study has three innovative aspects. First, this study will be one of the first to test the impact of multilevel implementation strategies on lung screening discussions and screening rates. We will test provider prompts that will serve as a reminder to discuss screening, and simultaneously target the patient level to address knowledge, communication, and psychological barriers to screening. It is well established that there are multiple levels of influence involved in lung screening; however, few studies have intervened beyond the individual level [24–27]. Second, the proposed study is applying the Health Disparities Research Framework to target two levels of influence, the patient-level and provider-level, that contribute to disparities in screening outcomes. This study is grounded in the disparities framework and these factors will be examined in moderation analyses. Finally, this study is testing the impact of implementation strategies aimed at the equitable adoption of lung cancer screening in diverse primary care practice settings. This study will examine the effect of these strategies on guideline-concordant provider-patient screening discussion and behaviors. The proposed strategies have the potential to increase adoption of this evidence-based intervention, improve outcomes, and mitigate racial disparities between African American and White patients who are eligible for lung screening.

This study will provide preliminary data on the effectiveness and feasibility of multilevel implementation strategies to improve lung screening utilization in an equitable manner. Future work will include a large 2 × 2 factorial, cluster randomized trial to compare the independent and overlapping contributions of the provider and patient implementation strategies. Study limitations include the quasi-experimental study design, which will limit the ability to determine causality. Second, we considered recruiting all potentially eligible patients irrespective of having an upcoming appointment, as those with a scheduled appointment may be sicker and/or more engaged in their healthcare. However, a primary endpoint is whether the provider-level prompt and the patient-level activation impact the discussion about lung screening at the clinical encounter, and so we elected to include an upcoming appointment as an eligibility criterion. It is well documented that the collection of smoking-related data (e.g., smoking duration, cigarettes per day, pack-years) in the EHR is not standardized and is often incomplete. The proposed study will use the EHR data to identify potentially eligible individuals based on age (50–80 years old) and smoking status (current and former). However, there will be a high number of screen failures as well as patients who may be eligible for lung screening but are not approached for the study due to data missingness. In other ongoing work, our research team is conducting a quality improvement project to improve how tobacco use is assessed and documented in the primary care setting across MedStar.

Following the successful completion of this study, future work will include partnering with an expanded number of primary care practices and utilizing a cluster randomized controlled trial to determine if these implementation approaches facilitate an increase in lung screening rates equitably.

## Data Availability

The datasets during and/or analyzed during the current study available from the corresponding author on reasonable request.

## Abbreviations

EHR: Electronic Health Record
USPSTF: United States Preventive Services Task Force
NLST: National Lung Screening Trial
African Americans: Black or African American individuals
Whites: White individuals
NIMHD: National Institute on Minority Health and Health Disparities
ERIC: Expert Recommendations for Implementing Change
PRISM: Practical, Robust, Implementation & Sustainability Model
RE-AIM: Reach, Effectiveness, Adoption, Implementation, Maintenance Framework
API: Application Programming Interface
GEE: Generalized Estimating Equations
